### 6.3. Populations for analyses

The data set will be analysed according to the ‘intention to treat’ (taking into account everyone who was assigned to an intervention arm) and ‘per protocol’ (taking into account only those who received  $\geq 75\%$  of the intervention, and the control group) principle.

### 6.4. Statistical analyses

#### General

For descriptive statistics, categorical data will be presented as percentages and counts, continuous data will be presented as means with standard deviations or medians with interquartile range in case of non normally distributed data.

For inferential statistics,  $\alpha$  will be set at 0.05, and 95% confidence intervals will be calculated. In case of multiple testing, a correction of the p-values will be used.

Covariates will be specified below and are selected based on theoretical knowledge.

Checks of assumptions will be performed, in case of non-normality, transformations of the variables or non-parametric tests will be used.

#### Primary outcome

For each cognitive test used, a selection of outcome measures will be used based on literature. Next, composite scores will be constructed for short-term memory (STM), long-term memory (LTM), executive functioning (EF) and processing speed (PS). The procedure for this is described below

The outcome measures, categorized by cognitive function:

| Short-term memory (STM)                           | Long-term memory (LTM)                          | Executive functioning (EF)                             | Processing speed (PS)        |
|---------------------------------------------------|-------------------------------------------------|--------------------------------------------------------|------------------------------|
| VRM free recall distinct stimuli (VRMFRDS)        | VRM delayed recognition total correct (VRMDRTC) | SWM strategy (SWMSX)                                   | RTI reaction time (RTIFMDRT) |
| VRM immediate recognition total correct (VRMIRTC) |                                                 | SWM between errors levels 4, 6, 8 and 12 (SWMBE46812)* |                              |
| PAL first attempt memory score (PALFAMS28)        |                                                 | OTS problems solved upon first choice (OTSPSFC)        |                              |
| PAL total errors (PALTEA28)                       |                                                 |                                                        |                              |
| DMS percentage correct (DMSPCAD)                  |                                                 |                                                        |                              |

\*SWMBE46812 is calculated by summing SWMBE4, SWMBE6, SWMBE8, SWMBE12

*STEP 1:* Create z-scores based on the pooled mean (across conditions), separately for each time point

*STEP 2:* Reverse-score the z-scores for the following outcome measures:

PALTEA

SWMSX

SWMBE46812

RTIFMDRT

*STEP 3:* Calculate the composite scores using the following formulas

$STM = (VRMDRDS + VRMIRC + PALFAMS28 + PALTEA28 + DMSPCAD)/5$

$LTM = VRMDRTC$

$EF = (SWMSX + SWMBE46812 + OTSPSFC)/3$

$PS = RTIFMDRT$

The outcomes are measured repeatedly at different time points, and are nested within individuals. This implies our data has a two-level structure, and this calls for an analysis technique taking into account the correlation between observations from the same person (Hoffman & Walters, 2022). Therefore, linear mixed models with random intercepts will be used, to take into account that each individual participant has a different starting point. Time (baseline, 3m, 6m and 12m) and condition (PA+CA, PA only, CG), and their interaction will be included as fixed effects.

Models with different levels of adjustment will be run: (1) crude model, (2) partially adjusted model including age, sex and education as covariates, and (3) fully adjusted model including age, sex, education, baseline PA and baseline CA as covariates. Model fit indices will be used to choose the models with the best fit.

In case of significant effects, post-hoc pairwise comparisons will be conducted to examine differences in the estimated marginal means of the outcome at T0, T1, T2 and T3 between 1) WALK+ vs. WALK-only and 2) WALK+ vs. CONT, but also the changes from T0 to T1, T0 to T2, T0 to T3, T1 to T2 and T2 to T3 for each group (WALK+, WALK-only and CONT). The p-values will be corrected for multiple testing.

The analysis will be conducted for the intention-to-treat and per protocol populations.

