## 2. Study design

To evaluate the effects of the cognitively enriched walking program on cognitive functioning (primary outcome), physical activity and psychosocial wellbeing (secondary outcomes), a randomized controlled trial (RCT) will be conducted. The intervention period will be 6 months, with measurements conducted at baseline, 3 months (mid-intervention), 6 months (post-intervention) and 12 months (follow-up). The interventions and measurements will take place at 2 university campuses in Belgium (Ghent and Leuven).

Participants will be allocated to one of the following intervention arms with a 1:1:1 allocation ratio: (1) cognitively enriched walking program, (2) walking program without enrichment, (3) passive control group. An investigator not involved in running the trial will generate the randomization sequence stratified by location (Ghent/Leuven) and availability (2 scheduling options for each location) using a statistical software program. Allocation will be disclosed to the researchers and participants only after completion of baseline measurements, ensuring double-blind data collection at baseline.

Furthermore, a process evaluation will be embedded in the RCT, using a mixed-methods design, and thus comprises questionnaires and focus group interviews. Questionnaires will be completed mid-intervention and post-intervention, focus groups will be conducted post-intervention.

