## 6. Statistical analysis plan

### 6.1. Hypotheses

#### Primary endpoint:

We hypothesize that the cognitively enriched walking program will have more beneficial effects on cognitive functioning compared to the other conditions at 6 months and 12 months.

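### Z-scoring each cognitive test separately at every visit removes change common to all arms, so the planned time effect and within-arm change tests show only change relative to the trial average; the between-arm comparison largely survives

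*Combined protocol and SAP*

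**What the plan says.** All references are to the combined protocol and SAP.

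- **Scoring (section 6.4, Primary outcome).** STEP 1 is "Create z-scores based on the pooled mean (across conditions), separately for each time point". STEP 2 reverses four measures. STEP 3 forms the STM, LTM, EF and PS composites from these z-scores alone.
- **Model (same section).** A linear mixed model with random intercepts is fitted to the composites: "Time (baseline, 3m, 6m and 12m) and condition (PA+CA, PA only, CG), and their interaction will be included as fixed effects".
- **Post-hoc tests (same section).** If effects are significant, two sets of tests follow. The first compares arms at each visit: "differences in the estimated marginal means of the outcome at T0, T1, T2 and T3 between 1) WALK+ vs. WALK-only and 2) WALK+ vs. CONT". The second looks at movement between visits inside every arm, and the plan words it as "but also the changes from T0 to T1, T0 to T2, T0 to T3, T1 to T2 and T2 to T3 for each group". P-values are to be corrected for multiplicity by a method that is not named.
- **Primary hypothesis (section 6.1).** It is a between-arm statement: the enriched programme is expected to have "more beneficial effects on cognitive functioning compared to the other conditions at 6 months and 12 months".

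STEP 1 names the pooled mean but not the SD. No section offers a raw-score or baseline-referenced version of the change tests.

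**The concern.** Re-centring at each visit and testing change between visits do not fit together. Once every visit's pooled mean has been set to zero, whatever the whole sample gained or lost is no longer in the data. A change within one arm is then that arm's change minus the trial's average change, yet the plan treats it as change in the arm itself.

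Five intervals in three arms give 5 x 3 = 15 such tests per composite, or 15 x 4 = 60 over the four composites, plus the time main effect. CANTAB is given at all four visits (section 5.3), so a shared practice or ageing effect is plausible. A control arm that improved less than average could be reported as declining, which would make the programme look protective. Equally, a programme arm that declined less than average could be reported as improving. Whether a gain was kept from T2 to T3 could not be read from these scores either.

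**Working it through.** **Inputs from the documents.** The scoring rule, model and contrasts are as set out above. There are three arms at 1:1:1 (section 2). Alpha is 0.05 (section 6.4, General); sidedness is not stated, so two-sided is taken. The plan gives no figure for the scoring step, so there is none to reproduce.

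**Assumed, because the documents do not give them.** Baseline SD 1; the true changes shown below; within-person correlation 0.7; 50 per arm (149/3 is about 50; 41 per arm, from 124/3, gave similar results); complete data; one baseline and one later visit; t tests of change in place of the mixed model; a visit-specific SD in STEP 1. The centring result does not depend on that SD.

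**1. Centring.** Let m(k,t) be the mean of arm k at visit t, and M(t) and S(t) the pooled mean and SD at that visit. The z-scored arm mean is (m(k,t) - M(t))/S(t). Averaged over all participants it is 0 at every visit, and so is any average of such z-scores, including the composites. With equal arms the three z-changes sum to zero.

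**2. Within-arm change.** With equal baselines and a stable within-arm SD of 1, for true changes c:

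z-change in arm k = (c(k) - mean(c)) / sqrt(1 + var(c))

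For c = (0.6, 0.3, 0.3): the mean is 0.4, the deviations are 0.2, -0.1, -0.1, and var = (0.04 + 0.01 + 0.01)/3 = 0.02. The divisor is sqrt(1.02) = 1.010, giving **+0.198, -0.099, -0.099**. Simulated means over 4,000 runs were +0.198, -0.100, -0.098, against +0.605, +0.302, +0.303 with baseline scaling.

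**3. Other assumed patterns (PA+CA / PA / control).**

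| True change | Reported under STEP 1 | Consequence (uncorrected tests) |
|---|---|---|
| +0.50 / +0.35 / +0.20 | +0.15 / 0.00 / -0.15 | Control estimate negative in 95% of runs, significant decline in 22%; with baseline scaling, significant gain in 43%, significant decline in none |
| +0.30 in all arms | 0 / 0 / 0 | Detection of the gain falls from about 77% to about 1% |
| -0.10 / -0.25 / -0.40 | +0.15 / 0.00 / -0.15 | Declining PA+CA arm shows a significant gain in 23% |
| +0.30 / 0 / 0 | +0.20 / -0.10 / -0.10 | Unchanged arms appear to decline |

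**4. False decline for c = (0.6, 0.3, 0.3).** With baseline scaling, the control arm's real gain was significant in 78% of runs; with STEP 1 it was significant in 0.03%. A false significant decline appeared in 9% of runs, and in 10.3% in a second run of 4,000. Requiring a significant arm effect first (approximated by an ANOVA of change) left 10.1%. Adding Bonferroni gave 3.8% over 3 tests, 2.5% over 5 and 0.9% over 15.

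**5. Between-arm contrasts.** (m(k,t) - M(t))/S(t) - (m(j,t) - M(t))/S(t) = (m(k,t) - m(j,t))/S(t). M(t) cancels. In the same scenario:

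- PA+CA minus control difference in change: 0.300 by visit, 0.304 by baseline.
- Power for that difference: 48.7% and 49.1%.
- Three-arm test of change significant: 50.1% and 50.2%.

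**6. If the SD moves.** S(t) does not cancel. For c = (0.50, 0.35, 0.20), var = (0.0225 + 0 + 0.0225)/3 = 0.015. The true difference of 0.30 becomes:

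- follow-up SD 0.8 times baseline: 0.30/sqrt(0.64 + 0.015) = 0.37
- follow-up SD 1.25 times baseline: 0.30/sqrt(1.5625 + 0.015) = 0.24

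**The case against.** The strongest reply is that the primary hypothesis does not need the affected tests. It concerns differences between arms at 6 and 12 months, and a centring constant common to the arms drops out of those differences and of the time-by-condition interaction. This stands. A reader might infer that the primary comparison is invalid; the documents do not support that, because section 6.1 asks a between-arm question and step 5 shows nearly the same estimate and power under both scorings.

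Other limits also stand:

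- Only change common to all arms is lost. A reader might infer that the composites can show no change at all, but an arm's change relative to the trial average is still visible.
- A wrong sign is conditional. It needs a true change between zero and the pooled change. If the pooled change is zero and SDs are stable, the within-arm tests are not biased.
- One arm's gain need not make each other arm appear to fall. Only the average of the others must; in the first row of the table PA stays at 0.00.
- The plan corrects these p-values, so 9-10% is an uncorrected rate. The correction method is not named, hence the range of about 1-4%.
- The assumed changes, correlation and SD ratios are not in the documents. With dropout, model-based visit means need not be exactly zero.

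The correction does not answer the point about estimation. It lowers the rate of false declarations but leaves the reported within-arm changes shifted by the pooled change. The requirement of a prior significant effect hardly helps, since it lets the tests run when arms differ, and then the re-centred arms take opposite signs.

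**Conclusion.** The point holds in limited form. That the time effect and within-arm changes lose the pooled change follows by algebra from STEP 1 with complete data, and no other section repairs it. The size depends on the true shared change, which the documents do not give. A shared gain or loss of a few tenths of an SD is enough to reverse the sign for an arm lying between zero and the pooled change.

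Primary between-arm inference largely survives. The remaining exposure there is one of unit: if STEP 1 uses a visit-specific SD and that SD changes, a true difference of 0.30 reads as about 0.24 to 0.37 for follow-up SDs of 1.25 to 0.8 times baseline, so differences at different visits are not on one scale.

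This is a should-fix matter, not one that overturns the primary analysis.

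**What to change.** Reword STEP 1 so that each test, at all four visits, is standardised with the pooled baseline mean and baseline SD of all randomised participants. Use the same constants for the intention-to-treat and per-protocol analyses, then apply STEPS 2 and 3 unchanged. This names the SD, keeps one unit across visits and restores absolute change: in the first row of the table the estimates return to +0.50, +0.35 and +0.20.

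If visit-specific scoring is kept, drop the within-arm change tests and state that the time main effect will not be interpreted. That resolves the centring problem, but a unit that can differ by visit remains.

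The cost is one sentence in the SAP and one line of code, with no new data. The change should be made before the outcome data are analysed.

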### **Secondary outcomes**

For physical activity, the Choi et al. (2011) algorithm will be used to define (non-)wear time. Next, the cutpoints of Barnett et al. (2016) will be used to determine time spent in moderate-to-vigorous physical activity.

Other outcomes will be processed as indicated in their corresponding manuals.

The same analysis as for the primary outcome will be used. The only difference will be the covariates: for physical activity these will be age and sex, for psychosocial wellbeing these will be age, sex and civil status.

The analysis will be conducted for the intention-to-treat and per protocol populations.

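### The four randomisation strata (location by availability) appear in no analysis model; adding them costs almost nothing and may tighten the between-arm comparisons at single visits

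*Combined protocol and SAP*

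**What the plan says.** Section 2 (Study design) has three arms "with a 1:1:1 allocation ratio" and has an independent investigator "generate the randomization sequence stratified by location (Ghent/Leuven) and availability (2 scheduling options for each location". Two locations with two scheduling options each make four strata. Blocking within strata is not described.

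Section 6.4 (Primary outcome) says that "linear mixed models with random intercepts will be used", with the participant as the only grouping level: "This implies our data has a two-level structure". The fixed effects are given as "Time (baseline, 3m, 6m and 12m) and condition (PA+CA, PA only, CG), and their interaction will be included as fixed effects". Three levels of adjustment follow: "1) crude model, (2) partially adjusted model including age, sex and education as covariates"; the third level adds the baseline values of physical and cognitive activity to that list. Fit indices then decide between them. If effects are significant, the post-hoc between-arm comparisons are of marginal means at each of the four visits (enriched walking against walking only, and against control). The changes over time that are listed are within each arm.

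Section 6.4 (Secondary outcomes) reuses this analysis with other covariates: "for physical activity these will be age and sex, for psychosocial wellbeing these will be age, sex and civil status".

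The General part of section 6.4 says that covariates are chosen on theoretical grounds. Location and availability are in no model, and no reason for leaving them out is given.

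**The concern.** A factor used to stratify randomisation normally belongs in the analysis. Stratifying makes the arms alike on that factor, so its effect largely drops out of the difference between arms. A model without the factor still counts its variance as residual, and so reports a standard error larger than the true one. Campus (a different measurement site) and schedule (possibly different kinds of participant) could plausibly be related to cognitive scores.

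At stake is precision on the only between-arm post-hoc contrasts that the plan names. The factors are known for everyone at randomisation, so any such loss is avoidable.

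**Working it through.** **Inputs from the documents.** Four strata and three arms (section 2); 149 to be recruited (section 6.2); walking groups of twelve or thirteen (section 4); four groups per active programme, two per city (section 5.2, Focus groups); alpha 0.05 (section 6.4, General), taken as two-sided. The plan gives no figure for the strata, so there is none to reproduce.

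**Assumed input.** The share of outcome variance explained by the four strata, R². The documents do not give it; 3%, 5% and 10% are used as a range.

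**Step 1: are arms likely to be balanced within strata?** 4 strata × 3 arms = 12 cells, and 149 / 12 = 12.4 per cell. This matches the planned group size and implies one group per active arm per stratum. Near-equal arms within strata are therefore what the plan expects, although blocking is not described.

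**Step 2: between-arm difference at one visit.** With n per arm, outcome variance σ² and balance within strata:
- true variance of the difference = 2σ²(1 − R²)/n
- variance reported without strata ≈ 2σ²/n
- ratio of reported to true SE = 1/√(1 − R²)
- actual type I error = 2Φ(−1.96/√(1 − R²))

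| Assumed R² | Reported SE / true SE | SE excess | Type I error |
|---|---|---|---|
| 3% | 1/√0.97 = 1.015 | 1.5% | 4.7% |
| 5% | 1/√0.95 = 1.026 | 2.6% | 4.4% |
| 10% | 1/√0.90 = 1.054 | 5.4% | 3.9% |

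**Step 3: check by simulation.** The plan's random-intercept model was simulated with 4 strata × 3 arms × 12 per cell, four visits, complete data, an assumed within-person correlation of 0.6 and 4,000 runs. At R² = 10%, for the single-visit contrast:
- without strata: mean model SE 0.204 against an empirical SE of 0.193; rejection rate under the null 0.036
- with strata: mean model SE 0.194; rejection rate 0.046

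The ratio 0.2043/0.1936 = 1.055 agrees with step 2. At R² = 0 the two models did not differ.

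**Step 4: change from baseline.** Baseline is one of the outcome visits and each participant has a random intercept. A stratum effect that is constant over time is the same at both visits and subtracts out. In the simulation the SE of the change contrast was 0.173 with and without strata at R² = 10%, and the two were identical at every R² tried. Additive stratum terms do nothing there.

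**Step 5: what this means for power.** Take 0.30 as a standardised mean difference (section 6.2 does not state the metric) and 124/3 = 41.3 per arm. Single-visit power for one pairwise contrast then rises from 27.0% to 28.7% at R² = 5%, and from 26.5% to 30.1% at R² = 10%.

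**The case against.** The strongest objection is that the contrasts which isolate the intervention effect do not suffer. Step 4 bears this out: with complete data the time-by-condition test and changes from baseline are untouched, and the marginal-mean comparisons are run only after a significant effect. This stands and limits the point. It does not remove it, because the single-visit differences are the between-arm comparisons that the plan names.

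The size is also assumed. Age, sex, education and baseline activity in the second and third models may already absorb part of any campus difference. Without blocking, the arms need not be balanced within strata, and the mismatch would be smaller or absent. Both points are fair; the planned group sizes only make near-balance plausible.

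A reader might infer three stronger things:
- **That the trial's tests are conservative overall.** Not shown. The two-level model also ignores the walking groups, which acts the other way. With 12.5 per group and an assumed intraclass correlation of 0.01, 0.02 or 0.05, the design effect 1 + 11.5 × ICC is 1.12, 1.23 or 1.58. The true SE for enriched walking against walking only is then about 6%, 11% or 25% above the model SE. The net direction is unknown.
- **That stratum terms would deal with group effects.** They would not. With one walking group per active arm per stratum, group coincides with the stratum-by-arm cell, so an additive stratum term leaves group effects unmodelled.
- **That the omission amounts to discarding participants in proportion to R².** That translation does not hold for the change contrasts, and R² is not known.

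**Conclusion.** The omission is plain in the text. Its consequence is modest and confined to between-arm marginal means at single visits and the overall condition effect. For these the reported SE is about 1.5% to 5.4% too large at an assumed R² of 3% to 10%, with type I error about 4.7% down to 3.9%. This rests on the strata being prognostic beyond the covariates already in the model, and on near-balance of arms within them; if the strata are not prognostic, nothing is lost.

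Taken alone, the omission does not inflate false positives. For changes from baseline and the time-by-condition test, only stratum-by-time terms could help, and only if strata differ in their course over time. The point is a free improvement, not a fault that threatens validity.

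**What to change.** In section 6.4, state that location and availability within location enter as fixed effects in every primary and secondary model, including the crude one. Say also that these terms stay in whatever the fit indices suggest, so that they cannot be dropped after the data are seen. Consider stratum-by-time terms as well, and record the decision before analysis.

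The cost is one sentence and 1 + 2 = 3 degrees of freedom; stratum-by-time terms would take a further 3 × 3 = 9. The data are known at randomisation. Clustering by walking group needs its own treatment and is not resolved by this change.

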### 3.3. Screening

Since the focus of this study is evaluating this program in cognitively and physically healthy older adults and cognitive functioning is our primary outcome, we decided to add two objective criteria to exclude participants that are more likely to have cognitive impairment. Firstly, participants with a score of less than 23 on the Montreal Cognitive Assessment tool (MoCA) will be excluded, as this might indicate (the beginning of) mild cognitive impairment (Carson et al., 2018). Additionally, we will exclude participants with a score of 20 and above (i.e. moderate to severe depression symptoms (Balsamo et al., 2018) on the Beck Depression Inventory (BDI-II), as depression can impact cognitive functioning (Köhler et al., 2010). Whenever participants are excluded because of a MoCA score below or BDI-II score above the cut-off, the participant will be informed about the deviant score by the either the PhD student (who has a MSc in Psychology and did an eight-month internship at a geriatric's department) or the postdoctoral researcher (who has a MSc and PhD in Psychology, took a course in psychogeriatrics, worked at a geriatric's department and works part-time as a primary care psychologist). Furthermore, the person will receive a letter that they can bring at their next appointment with their general practitioner. The letter will (1) contain the description of the test and the score obtained and an explanation that there are multiple possible reasons for such a score, and that only one of them is (mild) cognitive impairment or depressive symptomatology and (2) indicate that, in case the general practitioner thinks this is necessary, an appointment can be made with a memory clinic or psychologist.

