### Baseline visit

First, the informed consent will be signed. At this moment, participants can also ask questions at the researcher if they have any after reading the information letter. During the baseline visit, the MoCA and BDI-II will be administered as a secondary screening for possible cognitive difficulties and depressive symptomatology, respectively. As mentioned above, participants excluded from the study at this stage will be informed about the deviant score by the either the PhD student or the postdoctoral researcher. Furthermore, the person will receive a letter that they can bring at their next appointment with their general practitioner. The letter will (1) contain the description of the test and the score obtained and an explanation that there are multiple possible reasons for such a score, and that only one of them is (mild) cognitive impairment or depressive symptomatology and (2)

indicate that, in case the general practitioner thinks this is necessary, an appointment can be made with a memory clinic or psychologist.

Included participants will be asked to provide sociodemographic information (i.e. age, gender, length, weight, nationality, country of origin, educational level, marital status, longest held profession, and income) during this baseline visit. Furthermore, participants will be asked if there is any relevant medical information the coaches need to know to ensure safety of the waling sessions (i.e., so the coach can anticipate any possibly dangerous situations).

Participants will also be asked to complete the questionnaires regarding cognitive function, psychosocial wellbeing, physical activity and general health described above (see *outcomes*). Objective cognitive and physical activity will be measured at baseline as well by administering the CANTAB and wearing an accelerometer for seven consecutive days (day + night), respectively. Participants will be asked to return the accelerometer by delivering it to the office of one of the researchers or by returning it by post (pre-paid by the research team).

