### 6.2. Sample size

An a priori power calculation was conducted in G\*Power 3.1. With an estimated effect size of 0.30 (average effect size for comparison between PA+CA and control across 3 meta-analyses of Zhu et al. (2016), Gavelin et

al. (2021) and Gheysen et al. (2018)),  $\alpha=0.05$ , power=0.80, a sample size of 124 would be sufficient to detect differences between the conditions. Assuming a 20% dropout rate, a total of 149 participants will be recruited.

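### Baseline MoCA and BDI-II are left out of every cognitive model; adding them could modestly tighten the 6- and 12-month between-arm contrasts, but not the condition-by-time test

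*Combined protocol and SAP*

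**What the plan says.** Section 6.4 (General) states the rule for adjustment: "Covariates will be specified below and are selected based on theoretical knowledge". Under Primary outcome it then names three models for each of the four cognitive composites: a crude model; one with age, sex and education; and a "fully adjusted model including age, sex, education, baseline PA and baseline CA as covariates". Fit indices decide between them.

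Two other baseline scores are available. Section 5.3 (Baseline visit) says: "During the baseline visit, the MoCA and BDI-II will be administered as a secondary screening for possible cognitive difficulties and depressive symptomatology". Section 2 withholds allocation until baseline measurement is finished. Section 3.3 excludes people with a MoCA below 23, as a possible sign of early impairment, and people with a BDI-II of 20 or more, "as depression can impact cognitive functioning". Neither score appears in any cognitive model, and no reason is given.

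The model is a random-intercept mixed model. Baseline is one of its four time levels, and it includes a condition-by-time interaction. If effects are significant, arms are compared pairwise on estimated marginal means at each visit. Changes between visits are examined only within each arm.

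**The concern.** The plan says covariates follow from theory, and it supplies a theoretical link to cognition for two measures taken on everyone who enters. It then uses neither. A baseline covariate that predicts the outcome removes between-person variance from a comparison of arms at a single visit. It also removes the part of a chance arm difference that runs through that covariate.

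This matters because the per-visit marginal-mean differences are the only between-arm pairwise comparisons planned for the 6- and 12-month hypothesis in Section 6.1. They do not subtract baseline, so with some 41 to 50 people per arm they are open to chance imbalance in global cognition. Section 6.4 (Baseline differences) compares arms on sociodemographic characteristics and outcome measures. MoCA is neither, so an imbalance in it need not be shown at all.

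**Working it through.** **Inputs from the documents.** Three arms, 1:1:1 (Section 2). Alpha "will be set at 0.05, and 95% confidence intervals will be calculated" (Section 6.4). From Section 6.2: "With an estimated effect size of 0.30"; "power=0.80, a sample size of 124 would be sufficient to detect differences between the conditions", so 124/3 ≈ 41 analysed per arm; "Assuming a 20% dropout rate, a total of 149 participants will be recruited", so 149/3 ≈ 50 recruited per arm.

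The plan gives no standard error or correlation for this point, so there is no figure of its own to reproduce. The 124 serves here only to set the arm size. It does not follow from the declared inputs, because the test family and the metric of 0.30 are not stated: a three-arm ANOVA with f = 0.30 gives 111 in total, and two arms with d = 0.30 need 175 each. That is a separate matter and does not affect the ratios below.

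**Assumptions.** Partial correlation r of MoCA with a composite, beyond the planned covariates: 0.2 to 0.4. Within-person correlation ρ: 0.5 to 0.8. The score enters as a main effect, as the plan's other covariates do. Units are SDs of the composite.

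**Step 1. Arm difference in marginal means at 6 months.** Without the score, SE = √(2/41) = 0.2209. With it, SE ≈ 0.2209 × √(1 − r²). The table sets this beside the generalised least squares SE for the planned model (3 × 41 people, four visits, complete data; ρ = 0.5 and 0.7 agree to rounding).

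| r | √(1 − r²) | SE by formula | SE from model | Fall (model) |
|---|---|---|---|---|
| 0.2 | 0.980 | 0.216 | 0.217 | 1.8% |
| 0.3 | 0.954 | 0.211 | 0.211 | 4.4% |
| 0.4 | 0.917 | 0.202 | 0.203 | about 8% |

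With 20% dropout the falls are 1.7%, 4.1% and about 7.6%. With complete data the same formula applies at 12 months. Reading 0.30 as a d, with 41 per arm and no multiplicity correction, power moves from 27.4% to about 28%, 30% or 32%.

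**Step 2. Arm difference in change from baseline to 6 months (condition by time).** SE = √(2/41) × √(2(1 − ρ)). This is 0.2209 at ρ = 0.5 and 0.2209 × √0.6 = 0.1711 at ρ = 0.7. The covariate adds the same amount to a person's baseline and 6-month values, so it drops out of the difference. Refitting with it leaves 0.2209 and 0.1711 unchanged. With 20% dropout the fall is at most 0.2%. The plan's own age, sex and education terms behave in the same way.

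**Step 3. If the model conditioned on the baseline composite.** The squared partial correlation remaining for MoCA is p² = r²(1 − ρ) / [(1 − r²)(1 + ρ)].
- r = 0.2, ρ = 0.8: 0.04 × 0.2 / (0.96 × 1.8) = 0.0046, SE ratio √(1 − p²) = 0.998.
- r = 0.4, ρ = 0.5: 0.16 × 0.5 / (0.84 × 1.5) = 0.0635, SE ratio 0.968.

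The further gain is therefore 0.2% to 3.2%. Conditioning on the baseline composite is itself the larger lever: its SE factor is √(1 − ρ²), or 0.80 at ρ = 0.6.

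**Step 4. Chance imbalance, per-visit contrasts only.** The standardised arm difference in a covariate has SD √(2/50) = 0.20 to √(2/41) = 0.22. A difference of 0.3 SD or more, in either direction, then arises in about 13% to 17% of trials for a given pair of arms. At r = 0.3 it shifts an unadjusted contrast by 0.3 × 0.3 = 0.09 SD, which is 30% of 0.30 if that figure is a d.

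**The case against.** The strongest reply is that the main test of the planned model loses nothing. A reader might infer that precision is being given away on the primary outcome as a whole. Step 2 shows otherwise: the interaction is untouched. Pairwise comparisons also run only after a significant effect, so if the interaction is the gate, the extra covariate does not help the trial through it. This stands, and it confines the point to the per-visit contrasts. The same holds for imbalance: a stable arm difference is removed when arms are compared on change, the plan contrasts arms at baseline, and BDI-II, as an outcome measure, is among the baseline comparisons.

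A reader might also infer that the SAP breaks its own rule on covariates. It does not. Section 3.3 justifies exclusion at a threshold; it does not commit the plan to adjust among people who pass it. Nor does it show that BDI-II scores below 20 predict CANTAB results, and no calculation here covers BDI-II. For MoCA, the restricted range and overlap with age and education point to a small r.

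A further tempting reading is that the plan prefers a covariate prone to missing data, since accelerometer weeks can be lost. Section 6.4 does not say whether baseline PA means the questionnaire or the accelerometer, so that cannot be concluded.

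What survives is that the per-visit contrasts are the planned between-arm answer at 6 and 12 months, and MoCA could improve them at almost no cost.

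**Conclusion.** The omission is real, its consequence is modest, and nothing in the planned analysis is invalid because of it. For the marginal-mean contrasts, the gain from MoCA is about 2% to 8% in SE. This rests entirely on an assumed r of 0.2 to 0.4, and the lower end is plausible. It shrinks to roughly 0.2% to 3% once the baseline composite is conditioned on, which the plan does not currently do. There is no material gain for condition by time. The protection against chance imbalance is likewise limited to the per-visit contrasts. For BDI-II the case is the plan's own rationale, without a figure. The point is an optional improvement.

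**What to change.** In Section 6.4 (Primary outcome), add baseline MoCA total as a pre-specified continuous covariate in the partially and fully adjusted models for all four composites. Baseline BDI-II total may be added in the same way, with a note that its contribution is unknown. State that the purpose is precision and balance in the per-visit marginal-mean contrasts, not the condition-by-time test. The benefit reaches the reported result only if an adjusted model is the one reported, which the section now leaves to fit indices.

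The cost is one line in the SAP and one or two model parameters per composite. No data beyond those already planned are needed. If the scores turn out not to predict, the loss is one or two degrees of freedom.
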